### Aim 3. To develop a predictive model to estimate patient-specific recurrence risk based on clinical, radiographic and echocardiographic characteristics in patients with PFO and CS. (Model #2)

For Aim 3 we will use Cox proportional hazard models to develop a predictive model to estimate patient-specific recurrence risk. Because patients with CS with higher PFO-related recurrence risk generally have a lower prevalence of conventional stroke risk factors[25], failure to adjust for general (non-PFO-related) recurrent risk can lead to paradoxical results. This has been a major challenge for prior studies, since the low rate of outcomes limits the statistical power to control for conventional stroke risk factors and model PFO-related risk. While in the RoPE study we will have many-fold the number of outcomes compared to any prior study, statistical power for this analysis remains an issue.

To address this, depending in part on the number of outcomes, we will consider a two-step approach, that takes advantage of the outcomes in the component of the RoPE database of CS patients *without *PFO. First, we will construct a model for recurrence risk on the component of the study of CS patients *without *PFO. Next, we will construct a model for recurrence risk on the component of the study of CS patients *with *PFO, using the derived risk variable from the first step to control for the confounding background risk of stroke from PFO-unrelated causes. This will permit background stroke risk to be controlled for in a statistically efficient fashion. For step two, using the study subjects with known PFO, we will pay particular attention to echocardiographic information (e.g. hypermobility of the interatrial septum, interatrial shunting at rest, severity of interatrial shunt, anatomical PFO size, presence/absence of spontaneous flow on color Doppler)--to identify features of "high-risk" PFOs.

Preliminary analyses for both phases of this two step process (i.e. modeling recurrence risk in patients without PFO and modeling recurrence risk in patients with PFO) will investigate associations between established risk factors and recurrent strokes. Kaplan-Meier survival curves and logrank tests will be used to assess statistical significance. For each phase, a multivariable prediction model for recurrent stroke will be developed using a Cox proportional hazard model, using an approach otherwise similar to that described for Aim 2. Predictive discrimination will be assessed using the overall C index [26]. Model calibration is assessed by comparing predicted survival probabilities against Kaplan-Meier (observed) probabilities across equal-sized risk quantiles (based on predicted recurrence probabilities). Differences between predicted and observed probabilities will be compared using a modified Hosmer-Lemeshow χ^2 ^statistic [27]. The Cox models be re-run including the study as a stratification factor to control for potential between-study differences in baseline survival functions when estimating hazard ratios of potential risk factors.

Adequacy of the data for Aim 3: Power was calculated on extreme optimistic and extreme pessimistic calculations. To obtain outcome rates for our sample we used databases with patients who had PFOs. We optimistically estimate available follow-up data for up to 1,752 patients with PFO; 1,332 from databases with both PFO and non-PFO patients and an additional 420 from databases that only have data on patients with PFOs. Based on the average outcome rates on the observed data, the estimated stroke rate for these patients is 6%. The sample size of 1,752 will provide 80% power to detect a clinically relevant hazard ratio of 1.77 for a risk factor with a prevalence of 50% and an overall stroke rate of 6%. Most pessimistically, we excluded 100% of our largest study (the German study [24]) and estimated follow-up will only be available for 70% of the remaining subjects which would result in a total sample size of 944. With this extremely conservative estimate of the sample size the study will have 80% power to detect a hazard ratio of 2.22 assuming an overall stroke rate of 6% and a risk factor prevalence of 50%.

While having a sample size toward this lower estimate would still be adequate to detect these moderate to large effects, it would require us to be parsimonious in testing variables to avoid over-fitting (only about 60 stroke outcomes in PFO patients). After final database construction, we will consider whether to model the risk of the composite outcome stroke and transient ischemic attack (TIA). This has an outcome rate of 11.2% on the sample of our database with completed follow-up, virtually doubling the number of outcomes.

### Aim 4. To develop a composite index that can rank patients with CS and PFO by their conditional probability that the PFO was pathogenically-related to the index stroke (Model #1) *and *the risk of stroke recurrence (Model #2)

For Aim 4, we will combine our probability models in order to stratify patients by their risk of stroke recurrence conditioned on the probability that the PFO is pathogenically-related (i.e. not incidental) to the index stroke. Thus, the aim of this step is to combine models to estimate the PFO-attributable recurrence risk. This step prepares us for Aim 5: stratification of the clinical trial populations by this attributable recurrence risk, which we hypothesize corresponds to stratification by expected-benefit. In performing Aim 5, it is important to recognize that subgroup analyses are prone to false positive results due to multiple comparisons. Indeed, an advantage of multivariable risk-based analysis is that it allows the influence of multiple variables to be summarized along a single dimension and thus minimize the risks of this Type I error. However, this is only the case if the stratification is *fully *specified, before the outcomes are examined, since even with a single risk model minor differences in stratification can influence results; when two risk models are combined, the potential for analytic flexibility-and therefore bias--is increased. While this Aim needs to be informed by the results of Aims 2 and 3, and the observed risk distributions in the RoPE populations, to emphasize the importance of *full pre*-specification of the stratification strategy, process and analysis before the outcome data of the randomized controlled trials (RCTs) are examined, we have partitioned this into a separate specific aim, to be completed before Aim 5.

A challenge of this step is that transformation of PFO propensity into a probability that a PFO is pathogenic versus incidental requires an estimate of the rate of PFO in a control population. The control rates of TEE-detected PFOs vary somewhat from study to study, presumably due to variation in TEE technique (since the presence of a PFO rates have been shown to be largely independent of patient characteristics in unselected [screened] populations[25,28]. Figure 1 shows the relationship of PFO propensity to the probability that a PFO is pathogenic under the assumptions that the control PFO rate is 15%, 20% and 25%. While the ranking of patients according to their probability that their PFO is pathogenically related to their index event is insensitive to the exact control rate selected, to converge on a control rate that would allow us to combine models #1 and #2, we will: 1) perform meta-analysis of control groups in prior case-control studies (CS versus non-cryptogenic stroke patients); 2) analyze the PFO-rate in TEE-studied non-cryptogenic stroke patients in component RoPE studies that included such patients (such as PICSS, which has 365 TEE-studied non-cryptogenic stroke patients). We will explore the distribution of the patient-specific probability that the discovered PFO is pathogenic across the different strata of the RoPE population.

Once the models are combined to produce the probability of stroke recurrence conditional on the probability that the index event was PFO-related (i.e. PFO-attributable recurrence risk), and based on a thorough understanding of the risk profile of the patients in the RoPE population and the randomized clinical trial population (but prior to any analysis of outcomes in the RCTs), the full stratification plan will be specified, as provisionally outlined in Aim 5.

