Precise determination of inclusion/exclusion criteria, specification of the independent variables and specification of the dependent variable for each of the models are dependent on careful examination of each of the component databases for details of variable definition and missingness. s Consensus on the variables will be reached among RoPE Investigators for the final models. Provisional variable descriptions are provided below.

The RoPE Study will include patients with CS who have been examined for the presence of a PFO with either TEE or Transcranial Doppler (TCD) and the injection of bubbles. The preliminary definition of CS for the RoPE Study conforms to the Trial of ORG 10172 in Acute Stroke Treatment (TOAST) classification,[20] and requires a "complete work-up" (defined below) for the cause of the stroke. Cardioembolic stroke in this classification was considered "probable" if there was a high-risk source of embolism and "possible" for medium risk sources. This latter category includes PFO and atrial septal aneurysms (ASA). For the purposes of the RoPE Study, subjects with medium risk sources will be considered cryptogenic. The definition of stroke for the RoPE Study is *"a sudden onset neurological deficit in a vascular territory presumed to be due to focal ischemia*." If the deficit lasts for less than 24 hours, it must be accompanied by acute magnetic resonance imaging (MRI) or computer tomography (CT) changes in appropriate locations. If the deficit is greater than 24 hours, MRI or CT changes are not required. *A "complete work-up" *must include: 1) MRI *or *CT; 2) Vascular imaging - catheter angiography or angiography by MRI or CT; 3) Cardiac rhythm study: at least one electrocardiography (ECG), or documented Holter or telemetry.

In addition to excluding patients with stroke of known cause, patients included in the RoPE study must be worked up for the presence of a PFO with a TEE using intravenous injection of bubbles. Patients can be included in model #1 without a TEE, if they have had both transthoracic echocardiography [to rule out other potential cardioembolic sources] and TCD with bubbles (to establish the presence/absence of right-to-left shunting). Only patients with a TEE will be included in Model #2, since this model will require assessment of the presence/absence of ASA and PFO grading.

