### Aim 2: To identify patient characteristics associated with the presence (versus the absence) of a PFO, and to use this "PFO propensity" to estimate the patient-specific probability that a PFO was pathogenically related to the index stroke. (Model #1)

Since PFOs discovered in patients with CS may be pathogenically related to the stroke or not, in Aim 2, we will use logistic regression models to identify patient characteristics that are associated with the presence of a PFO among patients with CS ("PFO propensity"). In previous work [7,11,21], we have shown that this "PFO propensity" can be related to the probability that a PFO is pathogenic (i.e. non-incidental) using Bayes' theorem and 2 simple assumptions: 1) if not for those strokes that are PFO-attributable, the probability of a PFO in a CS patient would be the same as in the general population (controls); and 2) the rate of PFO-attributable strokes in PFO-negative CS patients is near-zero. Under these conditions:

Since the patient-specific probability of PFO in CS is given by the PFO propensity (i.e. the prevalence of PFO in CS patients otherwise similar to the patient), the only additional term needed to estimate the probability that a PFO is incidental for a particular patient is the general rate of PFO in the population (PFO probability in controls).

To develop a predictive model for PFO propensity, we will explore crude associations (overall and within each database) between the presence of a PFO and clinical variables including the subject's age, gender, race, hypertension, diabetes, hyperlipidemia, history of prior episodes of cerebral ischemia, obesity, antithrombotic medications, concurrent deep venous thrombosis, and neuroradiologic variables (i.e. prior stroke on MRI or CT, small [< 1.5 cm] versus large infarct, location of infarct). Multivariable associations between predictors and the presence of a PFO will be examined using logistic regression models. Selection of candidate variables for these models will be based on clinical rationale and the published literature. Variables with statistically marginal associations in the preliminary analyses (p > 0.15) will be removed. Non-linear associations between independent risk variables and the outcome will be investigated using generalized additive spline models[22]. As indicated, appropriate parametric logistic regression models will be developed to capture these non-linear relationships.

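### Model 1 may pool TEE- and TCD-detected PFO, but one essentially TEE-based control rate converts it; the conversion has no floor at zero, and the composite index depends on that rate

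*Protocol article*

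**What the plan says.** All references are to the protocol article.

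- **Aim 1, eligibility.** The study takes patients "examined for the presence of a PFO with either TEE or Transcranial Doppler (TCD) and the injection of bubbles". TEE is then made the norm, with an exception: "Patients can be included in model #1 without a TEE, if they have had both transthoracic echocardiography" and a TCD bubble study. The second model has no such exception: "Only patients with a TEE will be included in Model #2".
- **Aim 2, conversion.** Propensity is converted by Bayes' theorem under two assumptions. The first is that, apart from PFO-attributable strokes, "the probability of a PFO in a CS patient would be the same as in the general population (controls"). The second is that PFO-negative patients have almost no PFO-attributable strokes. Given these, "the only additional term needed to estimate the probability that a PFO is incidental for a particular patient is the general rate of PFO".
- **Aim 2, modelling.** The model is refitted in each database, study-by-predictor interactions are examined, and the final fit has a random study effect. No term for detection method is stated.
- **Aim 4, control rate.** The conversion "requires an estimate of the rate of PFO in a control population. The control rates of TEE-detected PFOs vary somewhat from study to study", and the article presumes that TEE technique explains this variation. It intends to settle on one rate from two sources: a meta-analysis of control groups in case-control studies (no method named) and TEE-studied non-cryptogenic stroke patients in the component studies. Figure 1 uses 15%, 20% and 25%. The ranking by probability of a pathogenic PFO "is insensitive to the exact control rate selected".
- **Aim 5.** The composite index enters the primary treatment-by-index interaction as a continuous variable.

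**The concern.** The conversion compares the odds of PFO in cases with the odds in controls. If the two are ascertained differently, a difference in detection is read as a difference in causation. The article itself regards technique as enough to move PFO rates between TEE studies, yet it lets a second modality into the case side only and states nothing that puts the two on one scale.

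Two further features of the same conversion matter for Aim 5, whatever the detection method. It is not bounded below by zero, and no rule is stated for propensities below the control rate. Also, once the attributable probability is combined with recurrence risk, the choice of control rate affects the order and spacing of patients on the index that carries the primary hypothesis.

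**Working it through.** **Formula.** The equation is not in the extracted text, so it is derived from the two assumptions. Let p be the PFO propensity in cryptogenic stroke and c the control rate. PFO-negative strokes (share 1-p) are all non-attributable. Among non-attributable strokes the odds of PFO are c/(1-c). Incidental PFOs therefore make up (1-p) × c/(1-c) of all patients, and

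AF(p, c) = 1 - [c/(1-c)] × [(1-p)/p].

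**1. The article's own statement.** The derivative of AF in p is [c/(1-c)]/p², which is positive for every c. Ranking by AF is therefore ranking by p at 15%, 20% or 25%, and the insensitivity statement is exactly right for Model 1. The level does move: at the overall propensity implied by Aim 2, 1,332/3,101 = 43.0%, AF is 0.77, 0.67 and 0.56 at the three rates.

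**2. Detection mismatch (the shifts are assumptions).** Take c = 25%, so c/(1-c) = 1/3, and TEE propensity 0.40.

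| Detection in cases relative to TEE | p | AF |
|---|---|---|
| 5 points lower | 0.35 | 1 - (0.65/0.35)/3 = 0.38 |
| equal | 0.40 | 1 - (0.60/0.40)/3 = 0.50 |
| 5 points higher | 0.45 | 1 - (0.55/0.45)/3 = 0.59 |
| 10 points higher | 0.50 | 1 - (0.50/0.50)/3 = 0.67 |

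This shifts the whole propensity. Model 1 would pool the methods, so dilution must be allowed for. Assume a true AF of 0.50, a TEE control rate of 20%, and a TCD control rate of 15%, 25% or 30%. With a true AF of 0.50 the case odds are twice the control odds, so p = 0.333 for TEE and 0.261, 0.400 or 0.462 for TCD. Mixing these p by the TCD-only share and converting at c = 20% gives:

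| TCD-only share (assumed) | TCD control 15% | 25% | 30% |
|---|---|---|---|
| 10% | 0.48 | 0.52 | 0.53 |
| 30% | 0.45 | 0.54 | 0.58 |
| 100% (TCD-only patients alone) | 0.29 | 0.63 | 0.71 |

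With a TCD control rate of 20%, every cell would be 0.50.

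**3. Negative values.** AF is below 0 exactly when p is below c. The lowest database prevalence in Table 1 is APRIS, 17/83 = 20.5%. AF there is 0.32 at c = 15%, 0.03 at 20%, and 1 - (0.795/0.205)/3 = -0.29 at 25%. Multiplied by recurrence risks of 6% and 3%, -0.293 gives -1.76% and -0.88%: below zero, the patient with the higher recurrence risk ranks lower.

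**4. Composite (product AF × recurrence risk assumed).** Patient A has p = 0.35 and risk 6%; patient B has p = 0.60 and risk 3%.

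| c | A | B | A - B |
|---|---|---|---|
| 15% | 0.672 × 6% = 4.03% | 0.882 × 3% = 2.65% | 1.38 |
| 20% | 0.536 × 6% = 3.21% | 0.833 × 3% = 2.50% | 0.71 |
| 25% | 0.381 × 6% = 2.29% | 0.778 × 3% = 2.33% | -0.05 |

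A wider pair (p = 0.30, risk 12% against p = 0.60, risk 5%) gives 7.1% v 4.4%, 5.0% v 4.2% and 2.7% v 3.9%. In a simulated population (p uniform on 0.26 to 0.70, log-normal risk around 6%, log-SD 0.5), 12% of pairs change order between c = 15% and 25%, or 19% if propensity and log risk correlate at about -0.5. These populations are assumed.

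**The case against.** Much can be said for the plan, and most of it stands.

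- A reader might infer that the insensitivity statement is wrong. It is not. It concerns the Model 1 ranking only, where step 1 confirms it, and the same sentence says that a rate must be settled before the models are combined. The article never calls the composite insensitive.
- A reader might infer that mixing TCD with TEE causes the negative values. It does not. They arise with TEE alone whenever p is below c. The APRIS figure is the mean of a small database (Wilson 95% interval about 13% to 30%), not a patient's propensity, and it is negative at only one of the three control rates.
- A reader might infer that Model 1 is shown to be biased. The article reports neither the TCD-only share nor TCD against TEE detection rates. With a 10% share and the range above, the pooled figure moves only from 0.50 to between 0.48 and 0.53.
- A reader might take the spread of PFO prevalence in Table 1 as evidence of technique differences. The table gives no detection method, and case mix, on which the whole approach rests, could produce it.
- The control rate is not simply labelled TEE: the meta-analysis source names no method.
- Fixing one control rate before the trial outcomes are examined is already planned in Aim 4.
- The random study effect and the study-by-predictor checks absorb some of the method difference where method follows database.

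The last point is only a partial answer. A study effect does not separate methods used within one database, and it does not place the propensity on the scale of the control rate. A source that names no method leaves the match open rather than securing it.

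**Conclusion.** The point holds in a limited form. The article allows a mixed TEE/TCD propensity to be converted with a single, essentially TEE-based control rate and states no detection-method term. The resulting bias is conditional: zero if the methods agree, otherwise of unknown size and sign. Under the assumed ranges, a true 0.50 becomes 0.29 to 0.71 in TCD-only patients, and 0.45 to 0.58 in a pool with 30% TCD-only.

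Two separate consequences do not depend on TCD. The conversion gives impossible negative values for any propensity below the control rate, which can occur within the article's own 15% to 25% range. The composite's order and spacing also vary with the control rate, which matters because Aim 5 uses the index as a continuous variable. The composite result rests on an assumed product form and illustrative patients. It is a consequence that the article leaves unaddressed, not a false statement in it.

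**What to change.** 1. Add detection method (TEE or TCD) to Model 1 and predict every propensity at TEE, or estimate the propensity in TEE patients only. Restrict the control-rate sources to TEE to match. If method turns out to vary only between databases, its effect cannot be separated from other study differences, and the TEE-only estimate is the cleaner choice.
2. Set the attributable probability to 0 where propensity is at or below the control rate, and say so when the index is specified in Aim 4.
3. Alongside the single control rate that Aim 4 already intends to fix, pre-specify that the primary Aim 5 interaction is repeated at 15%, 20% and 25%, the Figure 1 values.

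The cost is one covariate or a somewhat smaller Model 1 sample, hence a slight loss of precision; some ties at zero on the index; and a few extra runs. No new data are needed beyond a record of the detection method for each patient.

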### Aim 5: To apply this score to patients in completed clinical trials (currently on-going) testing percutaneous PFO closure against medical therapy, from low-expected-benefit to high-expected-benefit

The primary hypothesis of Aim 5 is that there will be a treatment-by-index interaction, when patients enrolled in RCTs testing PFO closure are ranked by their risk of stroke recurrence, conditioned on the probability that the PFO was pathogenically-related to the index event (using the composite index as a continuous variable). A p-value of 0.05 will be the threshold for significance. Depending on results, a clinically usable model will be developed. This step comprises external validation of the combined model. In addition, model 2 (the CS recurrence risk model) will be externally validated on the pooled medical arms of the RCTs by conventional criteria, including goodness-of-fit tests, ROC curve areas and calibration plots as described in the prior aims.

For Aim 5, we have, as of this writing, received agreement to test the risk models on two RCT databases, which will be pooled. Additional RCTs will be sought. The two RCTs to be pooled are:

Randomized Evaluation of Recurrent Stroke comparing PFO Closure to Established Current Standard of Care Treatment (RESPECT) Trial: (http://ClinicalTrials.gov identifier: NCT00465270) This is a prospective, randomized, multi-center trial, enrolling at 60 North American centers, designed to investigate whether percutaneous PFO closure with the Amplatzer PFO Occluder is superior to current standard of care medical treatment in the prevention of recurrent stroke. Inclusion criteria include age of 18-60 years old, cryptogenic stroke (not TIA) within 270 days, and TEE demonstration of a PFO. The recruitment target is 1000 subjects who will be randomized 1:1 to endovascular PFO closure or medical management. The primary endpoints are recurrence of non-fatal stroke, post-randomization death, and fatal ischemic stroke.

PC-Trial: Patent Foramen Ovale and Cryptogenic Embolism: (ClinicalTrials.gov identifier: NCT00166257). The PC-Trial is very similar in design to the RESPECT Trial comparing the efficacy of percutaneous PFO closure with medical treatment in 26 European centers. An additional inclusion criterion is cryptogenic peripheral embolism. Subjects are being stratified according to age and presence or absence of an atrial septal aneurysm. The recruitment target is 410 and the primary outcome is death, non-fatal stroke and peripheral embolism[29].

Adequacy of the Data for Aim 5: The proposed sample of 1400 subjects from RESPECT and the PC-Trial will provide sufficient power to detect a moderate interaction in the association of the recurrent risk stratification and the two study treatment groups. Power was estimated through simulations in SAS across multiple parameter configurations. For example, the proposed study sample of 700 subjects in each study arm, with an overall recurrence rate of 5% (stroke only), will provide approximately 80% power to detect a difference in the hazard ratio for a change of 10% in predicted risk of 1.00 and 1.33 for the two study groups, assuming a uniform distribution of risk scores. Additional RCTs will also be sought.

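### The only formal calibration measure named for validating Model #2 is a grouped chi-square test, and on about 35 strokes a non-significant result would be weak evidence of calibration

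*Protocol article*

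**What the plan says.** In the protocol article, Aim 5 first tests a treatment-by-index interaction in the pooled trials. It then adds that Model #2 "will be externally validated on the pooled medical arms of the RCTs by conventional criteria, including goodness-of-fit tests, ROC curve areas and calibration plots", as set out for the earlier aims. The list is open and has three members.

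The earlier aim that deals with the Cox model is Aim 3. There, "Model calibration is assessed by comparing predicted survival probabilities against Kaplan-Meier (observed) probabilities across equal-sized risk quantiles", and "Differences between predicted and observed probabilities will be compared using a modified Hosmer-Lemeshow" chi-square statistic. Discrimination is covered by the C index. The number of quantiles, the degrees of freedom and the significance level of the fit test are not stated.

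The size of the validation sample follows from the paragraph on adequacy of the data for Aim 5, which refers to "the proposed study sample of 700 subjects in each study arm, with an overall recurrence rate of 5% (stroke only" recurrence). The one threshold in Aim 5, "A p-value of 0.05 will be the threshold for significance", belongs to the interaction hypothesis. The power statement there also concerns only the interaction.

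**The concern.** ROC area and C index measure discrimination. They do not change if every predicted risk is inflated by the same factor. Whether the absolute risks are right is therefore left to the plots and the predicted-versus-Kaplan-Meier comparison, which carry no summary number, and to the grouped chi-square, which is the only formal measure.

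A grouped fit test answers only whether misfit was detected. It gives no estimate of the size of the misfit and no interval, and with few events it detects little. If a non-significant result were reported as successful validation, a recurrence model with materially wrong risks could go forward.

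This matters because Aim 4 combines Model #2's risk with Model #1 to estimate PFO-attributable recurrence risk, and the Background gives the goal as informing patient selection for closure. The Background also puts average recurrence at about 2% per year and warns that rare complications could cancel the benefit. Aim 3 itself names over-fitting as a danger at the lower sample size (about 60 strokes in PFO patients), and over-fitting is what produces too-extreme predictions.

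**Working it through.** **The plan's own figure.** The article gives no event count or power for validating Model #2. Its Aim 5 figure is about 80% power for the interaction. That cannot be confirmed exactly, because the range of the uniform score is not given: simulation gives 72% for a range of 0-80% and 89% for 0-100%, which bracket it.

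**Events.** The first trial: "The recruitment target is 1000 subjects who will be randomized 1:1 to endovascular PFO closure or medical management", so 500 medical. The second: "The recruitment target is 410", about 205 medical if also 1:1 (not stated). Together that is about 705, against 700 in the power paragraph. Strokes: 700 × 0.05 = 35 (705 × 0.05 = 35.3). Per group: 35/4 = 8.75, 35/5 = 7, 35/10 = 3.5.

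**Assumptions not in the article.** Level 0.05 for the fit test; true logit risk normal with SD 0.7 and mean risk 5%; complete follow-up; 4, 5 or 10 equal groups; degrees of freedom g−1 to g. Statistic: sum over groups of (O−E)² / [n p(1−p)], with p the predicted risk.

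**Why grouping matters (rough hand check, Poisson variances).** With 1.5-fold over-prediction, E = 1.5 × 35 = 52.5. The systematic part of the statistic totals (52.5−35)²/52.5 = 5.83 however many groups are used. Each group adds noise of about 35/52.5 = 0.67. The 5% critical value rises faster than that:

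| Groups | Expected statistic | Critical value, g−1 / g df |
|---|---|---|
| 4 | 4 × 0.67 + 5.83 = 8.5 | 7.81 / 9.49 |
| 5 | 5 × 0.67 + 5.83 = 9.2 | 9.49 / 11.07 |
| 10 | 10 × 0.67 + 5.83 = 12.5 | 16.92 / 18.31 |

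**Simulated chance of missing the error (p ≥ 0.05), g−1 to g df.**

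| Error in Model #2 | 4 groups | 5 groups | 10 groups |
|---|---|---|---|
| 1.5-fold over-prediction | 40-55% | 50-64% | 79-85% |
| Slope 0.7 (too extreme) | about 65-74% over all three groupings | | |
| 1.25-fold over-prediction | 82-97% over all three groupings | | |

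At g−1 degrees of freedom a correct model is rejected in about 8-9% of runs. For slope 0.7, varying the assumed SD from 0.5 to 1.0 gives 49-84%.

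**Direct observed/expected test on the same data.** By hand: reject if O is below 52.5 − 1.96 × √52.5 = 38.3. With O Poisson with mean 35, P(O ≤ 38) is about 0.73, a miss rate of 27%. With binomial variances the simulations centre on about 23% (range 20-27%). This test addresses overall over- or under-prediction only; a slope error needs the calibration slope.

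**Precision of observed/expected with 35 events.** exp(1.96/√35) = exp(0.331) = 1.39, so a ratio of 1.0 has a 95% CI of about 0.72 to 1.39. A ratio of 35/52.5 = 0.67 has 0.67/1.39 = 0.48 to 0.67 × 1.39 = 0.93, which excludes 1.

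**Sensitivity to the event rate (1.5-fold over-prediction).** With 10 groups and 9 df, the miss rate is 67% at a medical-arm risk of 6%, 54% at 7%, and 93% if the true risk is 3.3% and the predicted risk 5%. With 5 groups and 4 df, the same three cases give 37%, 26% and 72%. Doubling the sample to 1,400 brings the 10-group figure to 34%.

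**The case against.** A reader might infer that a model with p > 0.05 is thereby passed as validated. The article does not say so. It has no pass/fail rule, it lists three criteria in an open list, and its 0.05 threshold concerns the interaction. Predicted-versus-Kaplan-Meier comparisons and plots are planned, and with 1.5-fold over-prediction the points would on average lie to one side of the line. This stands, and it limits the point to how a non-significant result could be read.

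A reader might also infer a fixed miss rate of about four in five. That needs ten groups, which the article does not specify; with five groups it is nearer one in two. This stands too.

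Uniform over-prediction does not by itself reorder patients if the index multiplies the two models' outputs, so Aim 5's ranking and interaction test would not be harmed by that error alone. Too-extreme predictions can reorder patients, because they change Model #2's weight against Model #1.

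The event count may rise: "Additional RCTs will also be sought", closure may work and leave a higher rate in the medical arms, and Aim 3 leaves open a stroke/TIA outcome (11.2% against 6%). The sensitivity figures show that this helps without removing the weakness. A version of the statistic using observed variances rejects the 1.5-fold error in 84-89% of runs, but it also rejects a correct model in 16-33%, so it is no rescue.

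Finally, calibration detail may sit in a fuller plan that is not shown. The number of groups and any acceptance margin are fairly left there. The choice of statistic is not a gap, because the article names it in Aim 3 and carries it into Aim 5.

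**Conclusion.** The point holds as an objection to a stated statistic. With about 35 strokes, a grouped chi-square misses a 1.5-fold over-prediction in roughly 40-85% of cases, depending on an unstated number of groups (4 to 10), and a slope of 0.7 in about 65-74%. A direct observed/expected test of the 1.5-fold error misses about 23%, so the data hold information that the named statistic uses poorly. Non-significance would be weak evidence of calibration under every grouping tabulated above.

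The figures rest on the assumed 0.05 level, SD of 0.7, complete follow-up and the overall 5% rate applied to the medical arms. They do not show that the plan would accept a miscalibrated model, since no acceptance rule is written and plots are also planned. Validation of Model #2 is secondary to the interaction analysis in Aim 5.

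**What to change.** - In Aim 5, report the observed/expected ratio (expected events from the Cox predictions) and the calibration slope, each with a 95% CI, as the main calibration measures beside the planned plots.
- Use the same two measures in Aim 3 ahead of the modified Hosmer-Lemeshow statistic.
- State that a non-significant Hosmer-Lemeshow test will not be taken as evidence of calibration.
- State that about 35 events leave roughly a 1.4-fold uncertainty in observed/expected, to be updated if more trials join.

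The cost is wording and a few lines of analysis on the same data and predictions. The downside is that the report may have to say that calibration of absolute risk is not firmly established.
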